### 3.5.3 Unblinding Protocol

This study adopts a two-step unblinding process. Once all Case Report Forms (CRFs) have been entered into the database and the statistical analysis plan is finalized following clarifications, verifications, and blind review, the database will be locked. At this stage, the first unblinding will take place, conducted jointly by the principal investigator of the study and the statistical personnel. During this step, the blind codes corresponding to each drug (Group A or Group B) will be revealed to facilitate grouping and statistical analysis of all data. After the analysis is completed, the second unblinding will be carried out by the principal investigator at the clinical research summary meeting, disclosing the treatment measures corresponding to Group A and Group B. Detailed records of all unblinding processes should be maintained.

## **4. Intervention**

### ***4.1 Drug Administration***

All eligible patients will be randomly assigned to either the experimental group or the control group. Both groups will receive conventional Western medical treatment according to the guidelines for coronary heart disease. Additionally, the experimental group will be treated with a clinically effective traditional Chinese medicine, named Qing-Xin-Jie-Yu Granules. The control group will receive a placebo treatment. The treatment period will last for 6 months, followed by a 12-month follow-up.

#### ***4.2 Drug Packaging***

Each participant's medication will be packaged in a large package, consisting of 3 medium packages and a convenience bag containing a 2-day reserve of medication. The dosage for one visit corresponds to one medium package, and the 2-day reserve dosage is separately packaged in a plastic convenience bag and stored inside the large package box. Both the large and medium packages must have labels affixed, indicating the drug number.

#### ***4.3 Drug Management***

Drugs should be uniformly managed and stored. The researchers will establish a clinical trial drug management record card to inspect the quantity, quality, and correctness of drug coding. The drugs will be dispensed, and their usage will be recorded by designated personnel. After the trial is completed, another designated person will be responsible for the collection and proper disposal of any remaining drugs.

#### ***4.4 Combination Drug.***

- 1) During the trial, participants are not allowed to take other traditional Chinese medicines used to treat coronary heart disease, atherosclerosis, or hyperlipidemia simultaneously.
- 2) If other medications are necessary for the treatment of other diseases, they can be continued. However, the names of the drugs (or other treatment methods), dosages, frequency of use, and timing must be documented in CRF for analysis and reporting.

### **5. Outcomes**

#### ***5.1 General information***

- 1) Demographic indicators: date of birth, gender, height, weight, ethnicity, occupation, body mass index (BMI), blood pressure.
- 2) General clinical data: present medical history, past medical history, smoking history, alcohol consumption history, and medication history.

The past medical history focuses on inquiring about early-onset cardiovascular disease family history (occurrence of the disease in first-degree relatives before the age of 55 in men and 65 in women), history of cerebrovascular disease, peripheral vascular disease, diabetes, hypertension, and dyslipidemia.

#### ***5.2 Efficacy outcomes***

### 5.2.1 Primary efficacy outcomes

- 1) CT-derived fractional flow reserve (CT-FFR).

### 5.2.2 Secondary efficacy outcomes

- 1) Imaging indicators measured by CCTA: the percentage of diameter stenosis (% DS), the percentage of area stenosis (% AS), coronary artery calcification score (CACS), and Gensini Score.
- 2) Seattle angina questionnaire (SAQ).
- 3) Inflammatory factors: high-sensitivity C-reactive protein (hs-CRP), matrix metalloproteinase-9 (MMP-9).
- 4) Blood lipids: total cholesterol (TC), triglycerides (TG), low-density lipoprotein cholesterol (LDL-C), high-density lipoprotein cholesterol (HDL-C), apolipoprotein A1 (Apo A1), Apolipoprotein B (Apo B) and lipoprotein (a) [Lp(a)].
- 5) Carotid artery ultrasound: carotid intima-media thickness (IMT) (mm), carotid plaque length  $\times$  thickness (mm), and carotid lumen stenosis (%).

## **5.3 Safety outcomes**

### 5.3.1 Primary safety outcome

- 1) the composite events of type 2, 3, or 5 bleeding as defined by the Bleeding Academic Research Consortium (BARC).

### 5.3.2 Secondary safety outcomes

- 1) Coagulation function: prothrombin time (PT), thrombin time (TT), international normalized ratio (INR), activated partial thromboplastin time (APTT).
- 2) Complete blood count: red blood cells (RBC), hemoglobin (HB), white blood cells (WBC), neutrophil percentage (NEUT%), platelets (PLT).
- 3) Urinalysis: urine protein (PRO), urine glucose (GLU), urine red blood cells, urine white blood cells.
- 4) Stool routine: white blood cells, fecal occult blood.
- 5) Liver function: alanine aminotransferase (ALT), aspartate aminotransferase (AST).
- 6) Renal function: blood urea nitrogen (BUN), uric acid (UA), serum creatinine (Scr).
- 7) Blood glucose.
- 8) Electrocardiogram.

## **5.4 Endpoint**

- 1) Major adverse cardiovascular events (MACE): non-fatal myocardial infarction, cardiovascular death, and revascularization.

## **6. Follow-up**

The treatment period will last for 6 months, and the follow-up will be a total of 12 months, with visits scheduled at the following time points: before treatment (visit 1),

2 months after treatment (visit 2), 4 months after treatment (visit 3), 6 months after treatment (visit 4), and 12 months after treatment (visit 5).

The process of discontinued case exiting the trial:

- a) Retrieve and record remaining drugs and packaging.
- b) Inquire about any adverse events or other relevant information.
- c) Perform a physical examination.
- d) Complete efficacy and safety evaluation.
- e) Record the reason for discontinuation.

## 7. Adverse events

### 7.1 Records of Adverse events.

Upon discovering an adverse event, the researcher should immediately document it in the original records and case report forms. If the adverse event qualifies as a serious adverse event, a new adverse drug reaction, or a severe adverse drug reaction, it should be reported following the appropriate procedures.

### 7.2 Judgment of Adverse events

#### 7.2.1 Severity Assessment

|          |                                                                                                                                                                                |
|----------|--------------------------------------------------------------------------------------------------------------------------------------------------------------------------------|
| Mild     | The subject can tolerate the adverse event, and it does not impact the treatment. No special treatment is required, and it has no effect on the subject's recovery.            |
| Moderate | The subject finds it difficult to tolerate the adverse event, and it may require discontinuation of the drug or special treatment. It directly affects the subject's recovery. |
| Severe   | The adverse event poses a threat to the subject's life, and it can result in death or disability. Immediate discontinuation of the drug or emergency treatment is required.    |

#### 7.2.2 Analysis method

According to China's "Measures for the Management of Adverse Drug Reaction Reporting and Monitoring", mainly following the five principles:

- a) Is there a reasonable temporal relationship between drug use and the occurrence of adverse reactions/events? Yes ☐ No ☐
- b) Does the reaction correspond to a known adverse reaction type of the drug? Yes ☐ No ☐ Unclear ☐
- c) After discontinuation or dose reduction, did the reaction/event disappear or decrease? Yes ☐ No ☐ Unclear ☐ Not discontinued or dose not reduced ☐
- d) After the suspected drug is used again, did the same reaction/event reoccur? Yes ☐ No ☐ Unclear ☐ Not used again ☐
- e) Can the reaction/event be explained by the effect of drugs, the progression of the patient's condition, or the influence of other treatments? Yes ☐ No ☐ Unclear ☐

### 7.2.3 Association Evaluation

Based on the five principles above, the association evaluation is classified into six levels: "Definite", "Very likely", "Probable", "Possible unrelated", "To be evaluated", and "Unable to evaluate". Among them, levels 1, 2, and 3 (Definite, Very likely, Probable) are considered as adverse drug reactions, indicating a certain or strong association with drug use. Other levels require further assessment or data collection to determine the association.

|                    | 1                                                       | 2 | 3   | 4 | 5   |
|--------------------|---------------------------------------------------------|---|-----|---|-----|
| Definite           | +                                                       | + | +   | + | -   |
| Very likely        | +                                                       | + | +   | ? | -   |
| Probable           | +                                                       | ± | ± ? | ? | ± ? |
| Possible unrelated | -                                                       | - | ± ? | ? | ± ? |
| To be evaluated    | There is a need for supplementary materials to evaluate |   |     |   |     |
| Unable to evaluate | The necessary information cannot be obtained            |   |     |   |     |

Noted: "+" indicates a positive association; "-" indicates a negative association; "±" indicates uncertain or difficult to determine; "?" indicates unclear or unknown association.

### 7.3 Outcomes of Adverse Event

|                                                  |                                                                                                                                                                                  |
|--------------------------------------------------|----------------------------------------------------------------------------------------------------------------------------------------------------------------------------------|
| Death                                            | The event leads to the end of life (the cause of death and time of death should be collected).                                                                                   |
| Not Recovered/
Not Resolved                   | After treatment, the adverse event's symptoms did not improve or recover.                                                                                                        |
| Recovered                                        | After treatment, the adverse event's symptoms completely disappeared, and there were no residual symptoms.                                                                       |
| Symptoms
Disappeared with
Residual Effects | After treatment, the adverse event's symptoms disappeared, but there are residual effects (the name or manifestation of the residual effect should be specified when recording). |
| Improved                                         | After treatment, the adverse event's symptoms improved.                                                                                                                          |
| Not Specified                                    | The situation is unknown, not followed up, recorded, or the subject refused to provide further information.                                                                      |

### 7.4 Reporting of Adverse Events:

General adverse events will be recorded in the CRF without the need for specific reporting.

Serious adverse events will be reported within 24 hours of becoming aware of the event, completing a Serious Adverse Event Report form, and submitted to National Medical Products Administration (NMPA), Drug Regulatory Authorities where the research center is located, Ethics Committee, and the sponsor. Written records of the report should also be retained.

## 8. Clinical Data Management

### 8.1 Electronic Data Management.

This study utilizes SQL Server 2000 to establish a database for data entry and

management. A designated individual is responsible for data management and confidentiality.

## ***8.2 Data Management Plan***

- 1) The Data Management Plan (DMP) will be authored by the Project Data Manager (PL).
- 2) Before the study commences, the Director of Data Management (DMD) will review the DMP to ensure it includes all the required steps and information.
- 3) The DMP must receive approval from the sponsor before implementation.

## ***8.3 Electronic Case Report Forms (eCRF)***

- 1) The PL will create the eCRF pages based on the paper-based CRF.
- 2) Once the pages are designed by PL, they will be handed over to another PL2 not involved in the current project for testing. After successful testing, PLs will submit an eCRF release application to the DMD.

## ***8.4 Data Entry***

- 1) Each center will have two clinical research associates (CRA) responsible for data entry.
- 2) The research data will be entered into the Drug Clinical Trial Data Management System of Xiyuan Hospital according to the scheduled follow-up time points.
- 3) Independent double data entry will be performed.
- 4) The eCRF is not considered the original record; its content is sourced from the original CRF.

## ***8.5 Data Verification and Cleaning***

### **8.5.1 Data Verification Plan**

The PL will develop a Data Verification Plan (DVP) based on the eCRF. The DVP should encompass thorough verification of primary and secondary efficacy outcomes, as well as critical safety indicators. Data verification should be conducted without knowledge of the treatment groups, and any data discrepancies or issues will be recorded in a Data Clarification Form (DCF).

### **8.5.2 Data Verification Methods**

- a) Source Data Verification (SDV). The monitor will log into the data monitoring section of the data management system at each research center to perform on-site verification. This involves a 100% check of the eCRF data against the source data.  
  
Any inconsistencies will be flagged and questioned online.
- b) System Automated Logic Checks. PL will analyze the DVP and identify portions suitable for automated system checks. Programs will be developed and integrated into the eCRF pages. During data entry, the computer will automatically verify these data to enhance data entry quality and data management efficiency.

- c) Manual Checks. Data that cannot be automatically verified by the computer will undergo manual online review. If any doubts arise during the process, they can be directly communicated by clicking on a query.

### ***8.6 Queries handling***

- 1) Issuing. Data entry personnel will regularly log into the system to download the Data Clarification Form (DCF) containing queries specific to their institution.
- 2) Answering. During the data cleaning process, PL or monitors will raise all data queries in the form of DCF. Researchers will be required to provide written responses and sign the DCF. Data modifications should only be made on the DCF, which will be preserved as the source document along with the original data in the research medical records.
- 3) Online Updates. Data entry personnel will perform online updates based on the responses provided in the DCF.
- 4) Resolution. PL or monitors will review the updated data until all queries are resolved.

### ***8.7 Data Review Meeting***

During the meeting, PL presents the data management status. And the sponsor, principal investigator, data management personnel, and statisticians collectively review unresolved data issues. According to the statistical plan, they discuss data set partitioning, verification of serious adverse event reports, and handling records.

Once a consensus is reached on all queries and data analysis set, and after updating the data based on the data review opinions, the data manager will lock the database upon receiving approval. The clean database will then be handed over to the statistical team.

### ***8.8 Database Locking and Unlocking***

#### ***8.8.1 Database Locking***

The database locking requires to fulfill the following prerequisites:

- a) All data has been correctly entered into the database.
- b) All data clarification forms have been resolved and incorporated into the database.
- c) The eCRFs have been reviewed and approved by the researchers.
- d) Medical coding has been completed.
- e) Final data and logical consistency checks have been performed and reviewed.
- f) Final review of evident errors or abnormalities has been conducted.
- g) All trial-related documents have been updated and saved in accordance with standard operating procedures.

After confirming that the trial meets the above criteria, PL submits a written request for database locking and obtains signatures from relevant trial personnel (including DMD, biostatisticians, clinical monitors, and principal investigators) on the written approval documents.

### 8.8.2 Database Unlocking

After the database has been locked, if any erroneous data is identified, PL submits a written request for unlocking along with the data audit findings. PL unlocks the database and revises the data according to the data audit findings. After the necessary revisions are made, the database is locked again. All revised data are traceable and maintain an audit trail.

## **9. Statistical Analysis**

All statistical tests will be conducted as two-tailed tests, and a P-value  $\leq 0.05$  will be considered statistically significant for the tested differences.

### ***9.1 Population for Statistical Analysis***

- 1) Intent-to-Treat (ITT) Analysis: All participants who express the intention to receive treatment and sign the informed consent form will be included in the analysis.
- 2) Full Analysis Set (FAS): This includes participants who signed the informed consent form, received the investigational drug at least once, and have corresponding efficacy indicator records. Baseline data analysis will focus on the FAS as the target population, and efficacy analysis will be based primarily on FAS results.
- 3) Per-Protocol Set (PPS): This includes participants who meet the inclusion criteria, do not meet the exclusion criteria, and complete the treatment regimen. PP analysis involves analyzing participants who adhere well to the trial protocol.
- 4) Safety Set (SS): This includes participants with safety indicator records. Missing values for safety indicators will not be estimated.

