### **2.4 Elimination criteria**

- 1) Cases where the patient selection violates the inclusion/exclusion criteria and should not have been randomized.
- 2) Subjects who do not cooperate with randomization or do not take any investigational drugs after randomization, or use drugs very minimally (<10%).
- 3) Cases where prohibited drugs were used, making it impossible to assess efficacy and safety.
- 4) No data available after randomization.

The decision to exclude such cases must be made during the blind review by the principal investigator, data manager, statistical analysis expert, and sponsor after discussion.

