### **2.5.2 Handling of dropout cases**

After a subject drops out, the investigator should maintain contact with the subject, inquire about the reasons for dropout, record the last medication administration time, and make the dropouts complete as many assessment items as possible. Then the CRF should be completed. If someone withdraws due to allergic reactions, adverse events, or ineffective treatment, the investigator should provide appropriate treatment measures and some form of financial compensation to ensure the subject's rights.

All enrolled cases, regardless of dropout status, should have their data recorded and retained in the CRF. These records are essential for the Full Analysis Set (FAS) analysis. Dropout cases do not need to be supplemented separately.

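### The primary analysis set hangs on an undefined efficacy record, conflicts with the elimination rules, and has no usable all-randomised set behind it

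*Protocol*

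**What the plan says.** Section 9.1 names four sets.

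- **FAS.** Participants must have signed consent, "received the investigational drug at least once, and have corresponding efficacy indicator records". Randomisation is not mentioned. This set is primary: "efficacy analysis will be based primarily on FAS results".
- **ITT.** "All participants who express the intention to receive treatment and sign the informed consent form will be included in the analysis". Section 9.2 assigns no analysis to it.
- **PPS.** Eligible participants who completed treatment.
- **Safety set.** Participants with safety records.

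Section 2.4 lists cases to be eliminated. One ground is eligibility: "Cases where the patient selection violates the inclusion/exclusion criteria and should not have been randomized". Another is taking no drug, or under 10% of it. A third is "Cases where prohibited drugs were used, making it impossible to assess efficacy and safety". The fourth is having no data after randomisation. The decision belongs to the blind review. No analysis set is named, and section 9.1 does not refer back to section 2.4.

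On dropouts, section 2.5.2 says "All enrolled cases, regardless of dropout status, should have their data recorded and retained in the CRF" and calls these records essential to the FAS. Section 2.5.1 takes the last primary result as final where baseline efficacy data exist. Section 9.2.1 multiply imputes missing efficacy data in the FAS.

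**The concern.** The primary comparison is protected by randomisation only if membership of the set does not depend on what happens afterwards. Here it can, by two routes: the efficacy-record condition in section 9.1, and the low-intake and prohibited-drug grounds in section 2.4.

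Neither kind of loss is likely to be unrelated to outcome. Section 2.5 withdraws patients for worsening condition, adverse events, poor compliance or prohibited drugs. Section 4.4 prohibits other traditional Chinese medicines for coronary disease, atherosclerosis or hyperlipidaemia, and a patient whose symptoms persist may be more likely to turn to one.

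As written, two competent statisticians could build different primary sets from the same locked data. The set that would normally serve as the reference, all randomised patients as allocated, is not defined anywhere in the protocol.

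**Working it through.** The point rests on wording. The plan gives no figure for set membership, so there is none to reproduce.

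**Step 1: which record?** Section 9.2.2 and the flow chart in section 12 place CT-FFR at baseline and Month 6 only.
- If the record is the Month-6 CT-FFR, patients without it leave the FAS. The imputation in section 9.2.1 then has no missing Month-6 CT-FFR to fill, and section 2.5.2 is defeated. I say essentially completers because sections 2.5.2 and 6 ask for assessments at exit, so some dropouts may have an early CT-FFR.
- If a baseline record, or any efficacy record such as the Month-2 SAQ, is enough, treated dropouts stay in and sections 2.5.1, 2.5.2 and 9.2.1 make sense.

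**Step 2: sections 9.1 and 2.4 side by side.**

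| Randomised patient | FAS by 9.1 | By 2.4 |
|---|---|---|
| No dose taken | Out | Eliminated |
| No data after randomisation | Depends on the record meant | Eliminated |
| Under 10% of drug, efficacy record present | In | Eliminated |
| Prohibited drug, judged not assessable, dose and record present | In | Eliminated |
| Ineligible, dose and record present | In | Eliminated |

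The last three rows conflict unless section 2.4 is confined to another set. Ineligibility is fixed before randomisation; low intake and prohibited drugs arise after it.

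**Step 3: ITT.** Section 4.1 says "All eligible patients will be randomly assigned to either the experimental group or the control group". Those randomised are therefore a subset of those who consent. A person who consents and then fails screening meets the ITT definition but has no arm.

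**Step 4: illustration of size.** Inputs from section 3.4: planned difference 0.92 − 0.77 = 0.15; margin 0.03; SD 0.13; maximum dropout 10%, which is 0.10 × 120 = 12 patients. Assumptions, not in the protocol: a fraction f of one arm is removed, the removed differ from those kept by a mean g, and the other arm is unaffected. The kept mean minus the all-randomised mean is f × g.
- f = 0.05, g = 0.05: 0.0025
- f = 0.10, g = 0.13: 0.013
- f = 0.10, g = 0.15 (removed active patients gain nothing): 0.15 − 0.9 × 0.15 = 0.15 − 0.135 = 0.015

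**Step 5: what imputation can restore.** If the removed 10% are dropouts with no Month-6 value, imputation under missing-at-random draws from completers in the same arm and gives about 0.9 × 0.15 + 0.1 × 0.15 = 0.15, not 0.135. If they are low-intake or prohibited-drug patients with an observed Month-6 CT-FFR, keeping them brings in their own values and gives 0.135.

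**Step 6: power.** With difference 0.15 − 0.03 = 0.12, SD 0.13 and two-sided 0.05, power is 99.9% at 60 per arm, 99.8% at 54 (10% removed) and 99.5% at 48 (20% removed). On the protocol's own inputs the issue is bias, not precision.

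**The case against.** The strongest reply is that the protocol shows what it means. Sections 2.5.1, 2.5.2 and 9.2.1 all keep dropouts in, so the completer reading is the one that fits worst. A reader might infer that the FAS is a completer set; the documents do not support that as fact. What stands is that section 9.1 permits the reading and nothing rules it out.

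Second, section 2.4 may have been meant for the PPS, and section 8.7 leaves the partition of data sets to a statistical plan that is not shown. But section 2.4 speaks of eliminating and excluding cases without limit, and the protocol has itself defined the FAS in terms that admit some of them. That is a conflict within the protocol, not detail left for later. The prohibited-drug ground is also narrower than any use: assessment must have become impossible.

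Third, the decision is made at blind review, before the first unblinding in section 3.5.3. This answers any suggestion that patients could be removed by known arm. It does not undo selection on events after randomisation.

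Fourth, leaving out patients who never took a dose is a common and mild restriction in a double-blind trial. I agree; the record condition and the section 2.4 grounds matter more.

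Fifth, an unused ITT set biases no result. That is correct. Its fault is that it leaves the plan without a usable all-randomised set.

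**Conclusion.** The point holds as an ambiguity and an internal conflict in who enters the primary analysis. Followed as written, the plan can select patients after randomisation.

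Its effect on the estimate cannot be derived from the documents. A reader might infer a bias of 0.015, half the margin. That figure needs the full 10% to be lost from the active arm, no gain at all among those lost, and no shift on placebo; no document figure supports the assumed zero gain. Even then the difference would be 0.135, still 0.105 above the margin. Nor would multiple imputation under missing-at-random by itself remove such a bias for dropouts whose outcomes are unobserved. The clearer gain comes from retaining low-intake, prohibited-drug and ineligible patients who do have Month-6 data.

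**What to change.** Before the blind review:

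1. Define the FAS (or a corrected ITT set) as all randomised patients, analysed in the assigned arm, whatever drug was taken and whether or not a Month-6 CT-FFR exists. Impute missing efficacy values by multiple imputation as in section 9.2.1. Section 2.5.1 carries the last result forward instead, so its wording must be brought into line.
2. State in section 2.4 that its exclusions apply to the PPS only, and refer to this in section 9.1.
3. Delete the consent-based ITT definition, or replace it with the all-randomised definition in item 1.

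The cost is protocol wording and a few imputed records, about 12 of 120 if dropout reaches the planned maximum. The estimate may be less favourable because low-intake and prohibited-drug patients are kept.
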